### Intervention process evaluation

2.4.

#### Design and procedure

2.4.1.

Process evaluation will rely on a mixed-methods approach, combining quantitative (i.e., questionnaires) and qualitative methods (e.g., focus groups). Students in the intervention group will participate in an initial qualitative assessment of their expectations and a final global assessment, in terms of their satisfaction with the intervention and intervention quality, using a questionnaire, with both closed questions (Likert-type scales) and open-ended questions. The program facilitators will also complete a session evaluation sheet at the end of each session, in order to check intervention fidelity. Additionally, sessions and program evaluation sheets will be applied immediately after each session to participants of the intervention group. At the end of the program, focus groups will be held with: (1) students from the three schools where the program will be implemented (one per intervention group); (2) three focus groups with parents (one per school); and (3) one focus group with teachers from the subject into which the program will be integrated and/or the class director (i.e., the teacher who is responsible for a particular class in school).

#### Instruments

2.4.2.

##### Session evaluation sheets

2.4.2.1.

Session evaluation sheets will be filled in after each session, both by intervention participants and facilitators. The students’ post-session evaluation questionnaires will include: (1) one item evaluating overall satisfaction with the session (i.e., “In general, did you like today’s session?”), answered on a Likert-type scale, ranging from 1 (“Did not like it”) to 4 (“Liked it very much”); (2) five items assessing the session’s perceived relevance (“Was the session important?”), interest (“Was the session interesting?”), and challenge (“Was the session challenging?”), as well as the degree to which the students feel they have developed their competences (“Do you feel that you have developed your skills?”) and whether they had difficulty in concentrating (“Did you feel difficulty in concentrating?”), all answered on a Likert-type scale ranging from 1 (“Not at all”) to 4 (“Very much”); and (3) two open-ended questions, where participants can mention the most and least appreciated aspects of the session (e.g., “What did you like the most in today’s session?”).

The sessions’ evaluation sheets completed by the facilitators to register relevant data at the end of each session (e.g., participants’ attendance, themes/contents covered, any deviations from the plan for each session) will be used to check intervention fidelity (i.e., whether the program is being implemented as planned). Their content will be discussed during the biweekly follow-up meetings with the project coordinator.

##### Overall program evaluation questionnaire

2.4.2.2.

At the end of the intervention, an overall intervention evaluation questionnaire will be applied to participants, including: (1) one item to collect a global assessment of the intervention, answered on a Likert-type scale ranging from 1 (“Did not like it”) to 4 (“Liked it very much”); (2) seven open-ended questions, with the purpose of identifying the program features and components that pleased the intervention participants the most and the least, what they consider to have learned, and their suggestions regarding changes that could be applied in future program implementations.

##### Focus group interview guides

2.4.2.3.

Semi-structured interview guides for the focus groups with participants, parents, and teachers will be structured around four main topics: (1) whether they consider the program to be beneficial; (2) what sessions, themes, activities, and components they (or their children/students) liked the most and the least, and why; (3) what they (or their children/ students) consider to have learned, and whether they perceived any changes in relation to the social and emotional skills targeted by the program (e.g., emotion regulation, communication), well-being, relationships with others, health literacy, and/or lifestyles; (4) suggestions regarding changes for future versions of the program (e.g., new contents and implementation logistics, such as scheduling, sessions duration and dynamics, etc.).

The interview guide for parents will also include questions regarding the usefulness of the program session dedicated to parents and their experiences with the activities that required the parents’ involvement (e.g., “challenges of the week” activities). The interview guide for teachers will also include questions regarding the adequacy of the integration of the program into a regular curricular subject (e.g., Citizenship and Development) and alternative forms of program implementation (e.g., as extracurricular activity).

#### Data analysis

2.4.3.

Descriptive statistics will be used to describe the evaluation of each session and of the overall program made by the participants. To determine whether specific sessions are perceived as being significantly more/less interesting, challenging, and relevant, whether participants perceived the session as contributing more/less to the development of new competencies, and whether they felt more/less difficulty in concentrating, analyses of variance (ANOVAs) will be conducted. Thematic analysis (Braun and Clarke, 2006) will be performed on all qualitative data gathered from the session evaluation sheets, overall program evaluation questionnaire, and focus groups transcriptions.

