Other themes related to positive psychology interventions are the subject of five sessions in particular. A special focus is placed on the theme of gratitude and empathy, highlighting the importance of positive interpersonal relationships and social connectedness for subjective well-being. The theme of subjective well-being is also present throughout the program, through the photo contest “Well-being-Promoting Actions,” as will be explained below. Finally, the video #CharacterStrengths introduces the theme referred to in its title during a session designed to help students to find their character strengths (Peterson and Seligman, 2004). Their “signature strengths” are then used to work on themes such as purpose in life, commitment, adaptability, and resilience.

Table 1 presents the summary of the main skills to be developed throughout the 20 sessions (19 sessions for adolescents and one session for parents) and the main activities for each session.

**Table 1 tab1:** Summary of the content of the sessions.

Session	Main skills to be developed	Main activities
#01 “Zero Street”	Subjective well-being	-Icebreaking with students: name one thing you like and another you do not like -Presentation of the program -Debate about “a better world” and suggestions for improving today’s world (e.g., What is the world like now? What would be the perfect world? What solutions exist? How can everyone contribute?) -Individual reflection on situations that contribute to well-being and for which each student is grateful
#02 “Health Roundabout”	Health literacy	-Debate about health (e.g., What does health mean to you? What makes you sick? What do you do to stay healthy?) and reliable information sources -Viewing of the video #HealthLiteracy -Discussion about the video: “What would you do in Maria’s situation?” -Reflection on the concept of overall health
#03 “Market of Emotions”	Emotion recognition	-“EmoImage”: identify the five basic emotions in images and classify them (sadness, anger, joy, fear, and disgust) -“Where do you feel emotions?”: drawing a body and painting where emotions are felt -Reflection on students’ perception of emotions and the differences and similarities between the paintings of the various groups

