#### Structure of sessions with students

2.2.3.

The sessions are implemented with groups of 12–15 students, with one facilitator per group. All sessions have clearly defined learning goals, and are dynamic and interactive, with a duration of 50 min (i.e., the same duration as regular curricular classes, in order to maximize the adolescents’ attention and encourage adoption of the program by creating the possibility of integrating it into regular curricular units). Most sessions are structured as follows: a semi-structured individual (or group) activity, a semi-structured activity in small groups, and a final interactive debate on what was learned during the session.

Although there are always one or two key skills that are the focus of each session, in the same session several competencies can be worked on, given their association with different themes and the use of different types of activities. For example, in session #14, titled “Parliament,” the main theme is communication (focusing on assertive communication as an important social and emotional skill); however, the themes covered in the scenarios presented to the students for the role-play concern different issues, such as (un)healthy behaviors, making it possible to work on health literacy at the same time.

At the end of each session, a “healthy tip” associated with the topic that was addressed during that session (e.g., #gratitude) is discussed and complemented with a “challenge of the week.” This challenge is an intersession activity to be developed during the week (e.g., “gratitude agenda”) and related to the content of the session. This activity can be shared and discussed at the next session if the participants so wish.

In the first session, each student will receive a folder in which to place all the activity sheets completed during the program. This folder will then serve as a portfolio and a record of the student’s evolution and involvement.

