#### Design and procedure

2.3.1.

A cluster randomized controlled trial design will be used for impact evaluation, with 8th grade classes (units of randomization) from three public schools being assigned to either the intervention or the control condition. Data collection will be based on structured questionnaires applied to all students, both in the control group and the intervention group. Baseline measures (T0) will be collected with all potential participants prior to intervention implementation. In each school, three classes will then be randomly selected to be part of the intervention group in Year 1, while the remaining classes will be the control group. Students who integrate the control group in Year 1 will be part of the Intervention Group in Year 2. The post-test (T1) will take place approximately 1 week after the end of the program and the follow-up (T2) will take place 9 months later.

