#### Data analysis

2.3.3

Descriptive statistics will be used to describe intervention and control group participants, replying to the pre-test, post-test, and follow-up questionnaires. To assess intervention effectiveness, statistically significant differences (and effect sizes) between the intervention and control groups will be examined by repeated measures ANOVA, contrasting results from the intervention and control groups (between-subjects factor) on the different outcome measures (e.g., social and emotional skills, health literacy, well-being) at pre-test, post-test, and follow-up (within-subjects factor).

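### The session comparisons name only ANOVA for ratings that are repeated within students and share one delivery per group; neither usual form of ANOVA is reliable for such data

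*Protocol article*

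**What the plan says.** Section 2.4.3 of the protocol article plans inference between sessions as well as description. The aim is stated as "To determine whether specific sessions are perceived as being significantly more/less interesting, challenging, and relevant", and the same for competence development and difficulty in concentrating. The method is given as "analyses of variance (ANOVAs) will be conducted". Neither the type of ANOVA nor an error term is stated. For the impact data, by contrast, section 2.3.3 says that group differences "will be examined by repeated measures ANOVA".

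The structure of the ratings is set out elsewhere:

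- Section 2.4.2.1: "Session evaluation sheets will be filled in after each session, both by intervention participants and facilitators". The student sheet includes "five items assessing the session’s perceived relevance" and the four other aspects, each on a 4-point scale.
- Section 2.2.1: the programme has "19 sessions for adolescents and one session for parents".
- Section 2.2.3: "The sessions are implemented with groups of 12–15 students, with one facilitator per group".
- Section 2.3.1: "In each school, three classes will then be randomly selected to be part of the intervention group in Year 1", from three schools.

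**The concern.** Two kinds of dependence follow from this structure. A student who rates generously tends to do so at every session, so the ratings of one student are correlated. And all students in a group rate the same delivery of a session by the same facilitator, so a delivery that went well or badly moves the whole group's ratings of that session together.

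The first kind inflates the error term of a one-way ANOVA and hides session differences. The second kind inflates the variation between session means, so a few facilitators' good or bad days can look like a property of the session. A repeated measures ANOVA by student removes the first problem and leaves the second. The article says that the process evaluation is to inform later programme adaptations, so a missed weak session or a falsely flagged one could carry into the revised programme.

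**Working it through.** The article gives no sample size, significance level or variance component for this analysis, so there is no figure to reproduce. The check asks how the two usual forms of ANOVA behave when no session truly differs.

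**Inputs from the article.** K = 19 student sessions; m = 12 to 15 students per group (13 used); 3 schools × 3 classes = 9 intervention classes in Year 1; 5 rated items.

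**Assumptions.** Two-sided 5% level; 9 to 18 delivery groups (the number is not given); complete ratings; total variance 1, split into student share vs, group-by-session share vgs, and residual ve = 1 − vs − vgs.

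**Expected mean squares with no session difference.**

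- Between sessions: ve + m·vgs.
- One-way error term: about 1, the total variance.
- Repeated measures by student, error term: about ve + vgs.

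Let r be the between-session mean square divided by the error term used. A calibrated test has r = 1. With many error degrees of freedom, the type I error is about P(χ² with 18 df > 28.87 / r), where 28.87 is the 5% point of χ² with 18 df. The number of groups hardly enters.

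**Numbers at m = 13.**

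| vs | vgs | ve | ve + 13·vgs | one-way: r, type I error | repeated measures by student: r, type I error |
|---|---|---|---|---|---|
| 0.30 | 0 | 0.70 | 0.70 | 0.70, 0.14% | 0.70/0.70 = 1.0, 5% |
| 0.40 | 0.02 | 0.58 | 0.84 | 0.84, 1.1% | 0.84/0.60 = 1.4, 30% |
| 0.40 | 0.05 | 0.55 | 1.20 | 1.20, 15% | 1.20/0.60 = 2.0, 70% |
| 0.40 | 0.10 | 0.50 | 1.80 | 1.80, 59% | 1.80/0.60 = 3.0, 94% |

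**Simulation.** With 9 and with 18 groups of 13, the same four settings gave:

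- one-way: 0.05% to 0.3%, 1.3% to 1.7%, about 15%, and 59% to 60%;
- repeated measures by student: 4% to 5%, 30% to 32%, 69% to 71%, and about 95%.

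**Group size.** At vgs = 0.05, repeated measures by student gives r = (0.55 + 12 × 0.05)/0.60 = 1.92 and 66% for m = 12, and r = (0.55 + 15 × 0.05)/0.60 = 2.17 and 77% for m = 15.

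**Power lost by one-way ANOVA.** By simulation, with a 40% student share, no group effects and one session shifted by 0.3 SD, power is 0.10 (9 groups) and 0.55 (18 groups). Repeated measures by student has 0.70 and 0.98.

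**Group-by-session error term.** A repeated measures ANOVA on group means had type I error of 4% to 6% in every scenario simulated.

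**Completeness.** If a repeated measures ANOVA keeps only complete records, and attendance is independent across sessions, 0.90^19 = 14% of students have all 19 ratings at 90% attendance and 0.95^19 = 38% at 95%. Both attendance rates are assumed. Absence concentrated in a few students would leave more complete records.

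**The case against.** The article does not say that the ANOVAs are one-way or that they treat ratings as independent. ANOVA is a family, and one member of it, the analysis of group means, is well calibrated here. A condensed article may also leave the error term of a secondary analysis to the full plan. This stands in part: the point cannot be that an independent-observations test has been fixed. It does not remove the point, because the two forms a reader would most naturally take from the text both fail in plausible settings, and carrying over the repeated measures ANOVA named for the impact data would not help if deliveries vary.

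A reader might infer that good and poor sessions will be wrongly identified. The documents do not support that. The direction and size of error depend on variance shares that they do not give. With student correlation alone, one-way ANOVA misses differences rather than inventing them, and repeated measures by student is close to nominal. Nor do the two forms always err in opposite directions: at group-by-session shares of 5% and 10% both reject too often.

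A reader might also infer that these tests decide which sessions are changed. They do not. Sections 2.4.2 and 2.4.3 add descriptive statistics, open-ended questions, thematic analysis and focus groups on which sessions were liked most and least, and no decision rule rests on a p-value.

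**Conclusion.** The concern holds in a limited form. Section 2.4.3 plans significance tests between sessions without a term for student or delivery group, although the ratings are repeated within students and share deliveries. One-way ANOVA is very conservative if student correlation dominates. Repeated measures ANOVA by student is reliable only if deliveries do not vary between groups; a group-by-session share of 2% is already enough to raise its type I error to about 30%.

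These figures rest on assumed variance shares, a 5% level and complete ratings from groups of 13. They change little between 9 and 18 groups. The matter is minor: it touches one of several inputs to programme refinement and leaves the effectiveness result alone.

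**What to change.** In section 2.4.3, replace the ANOVAs with one mixed model per rated item: session as a fixed effect; random effects for student, group and group-by-session; all available ratings used. A simpler alternative is a repeated measures ANOVA on group-by-session means. The choice of multiplicity adjustment can be left to the analysts.

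State that the rating sheets carry a student code, or at least a group code if the group-means version is used. The article does not say whether they do, and without a code neither analysis is possible.

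The cost is a few sentences of analysis wording, slightly more analysis work and a code on the sheet. If the sheets are at present anonymous, which the article does not say, a student code would make the ratings pseudonymous, and some students may answer less freely.

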## Dissemination

3.

The plan for disseminating the #EntreViagenseAprendizagens program includes the following measures: (a) publish the results on the effectiveness of the intervention program in peer-reviewed journals; (b) write a technical manual (including all videos and activity sheets to be used) to ensure that the program is implemented in the same way by different facilitators and with different groups; and (c) train program facilitators, through workshops on the theoretical rationale and methods for the implementation of #EntreViagenseAprendizagens in schools, targeting teachers, psychologists and other school and mental health professionals who want to implement this program with adolescents.

## Discussion

4.

The aim of the present paper is two-fold: to describe the content of a school-based intervention designed to promote adolescent well-being through the development of social and emotional skills, health literacy, and healthy lifestyles in 8th and 9th grade students; and to present its evaluation protocol. Despite the numerous school-based interventions focused on social and emotional skills, mental health, and healthy lifestyles, or even specific school-based positive psychology interventions, there have been few interventions aimed at promoting the well-being of adolescents in such a comprehensive way, considering all its dimensions. #EntreViagenseAprendizagens is innovative, since it is a multi-component school-based intervention that takes into account the adolescents’ overall well-being, including their mental and physical health and well-being, alongside character strengths and social and emotional skills, all of which are essential to their future adaptation in a continuously changing world. This is a relevant fact, considering that multi-component interventions are in line with the most recent conceptualizations of adolescent well-being (Ross et al., 2020) and of health-promoting schools (World Health Organization and United Nations Educational, Scientific and Cultural Organization, 2021).

The development of the program is based on solid intervention approaches that have shown promising results, such as social and emotional learning (CASEL, 2020), health literacy promotion (Bröder and Carvalho, 2019), and positive psychology interventions (Seligman et al., 2009). Moreover, the use of an experimental design with pre- and post-intervention measurements for impact evaluation will make it possible to provide solid evidence on the effectiveness of the intervention. If the expected results are achieved, future research should continue to investigate this intervention and its mechanisms for action by standardizing its design. Furthermore, process evaluation based on the use of mixed methods will provide insights into contextual factors and mechanisms that may impact the overall intervention effects, informing future program adaptations, if needed.

It is urgent to invest in a whole-school approach, with the integration of #EntreViagenseAprendizagens and other similar programs into the compulsory school curriculum, which can be adapted to the specific needs of each group of students and allow for the development of real health-promoting schools (World Health Organization and United Nations Educational, Scientific and Cultural Organization, 2021).

## Data availability statement

The original contributions presented in the study are included in the article, and further inquiries can be directed to the corresponding author.

